### Statistical analysis

The primary analyses will be conducted using the intention-to-treat principle. Fall data will be analysed using all randomised participants until they have died or have withdrawn from the study. Demographic and clinical characteristics at baseline will be summarized with descriptive statistics. The incidence of falls with 95% confidence intervals (CIs) in the two groups (intervention group and control group) will be calculated and compared using negative binomial regression analysis. The proportion of fallers in the two groups will be compared with the relative risk statistic. General linear models will be used to assess the effect of group allocation on the continuously-scored secondary outcome measures after adjusting for baseline scores. Logistic regression models will be used to compare groups on dichotomous outcome measures. Interactions between subgroup variables (past falls and mobility-related disability) and group allocation will be tested, and in the case of a significant interaction, the comparison between the intervention group and control group will be reported within the subgroups. Statistical analyses will be undertaken using the SPSS and Stata software packages. P < .05 will be considered statistically significant.

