## Methods

### Trial design

This study is a multicentre parallel-group RCT with 12 months follow-up (Figure 1). The Human Ethics Committee of the University of São Paulo Faculty of Medicine Clinics Hospital (CAPPesq 0145/11) has approved the trial and all participants will give written informed consent. Participants will be randomly allocated to either a “usual care” control group or the ‘multifactorial falls prevention program” intervention group. Eligible participants will be randomly allocated to study groups after the completion of a baseline assessment. The maximum estimated length between the baseline assessment and the randomisation will be 3 months.Group allocation will take place centrally using a computer-generated permuted block randomisation schedule by an investigator not otherwise involved in recruitment or data collection (i.e., a concealed randomisation system). Assessors will be blinded to group allocation but due to the nature of the trial, the participants will not be blinded to group allocation.

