### Participants

Community-dwelling men and women aged 60 and over who have fallen at least once in the last 12 months will be included. A fall will be defined as “an unexpected event in which the participants come to rest on the ground, floor, or lower level.” Participants will be asked to answer the question: “In the past 12 months, have you had any fall including a slip or trip in which you lost your balance and landed on the floor or ground or lower level?” [26].

At initial contact potential participants will be screened by telephone to ensure they have fallen at least once in the past 12 months and will be able to attend the evaluation centre once a week for 12 weeks. If there is an affirmative answer to both questions, the person will be invited to attend the evaluation centre to be assessed for eligibility.

Participants will be excluded if they have:

• A previous diagnosis of dementia or a cognitive decline that prevents the understanding of simple instructions or guidelines;

• A previous stroke with a severe neurological impairment, such as loss of strength, and perceptual or language limitations;

• A progressive neurological disease (e.g. severe Parkinson’s disease);

• A severe visual deficiency;

• Any acute illness that the physician considers as an exercise contra-indication (e.g. uncontrolled angina, acute coronary disease);

• An acute vertigo or dizziness less than3 months duration;

• Inability to maintain a standing position, even with the use of a walking aid or other device.

Participants will also be excluded if they unable to communicate due to an aphasia, severe hearing loss even with the use of hearing aids or those who do not have mastery in Portuguese language. People will also be excluded from participation if they are engaged in a regular exercise program that is likely to challenge balance, including physical therapy, with a frequency of equal to or more than twice a week such as: muscle strengthening, balance or gait exercise, Tai Chi and Yoga. People will not be excluded if their regular exercise regime is limited to walking, water-based exercise or any other form of therapy that does not include the exercises described above (e.g., thermotherapy, spine and shoulder exercises, etc.).

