### Setting and recruitment

Participants will be recruited in 4 referral centers in Sao Paulo, Brazil (Geriatrics Service at the University of São Paulo Faculty of Medicine Clinics Hospital; the Institute of Geriatrics and Gerontology “José Ermírio de Moraes”; the Reference Centre for the Elderly in the North Zone and the Paula Souza Primary Care Centre).

The Faculty of Medicine Clinics Hospital is a public complex of health institutions which offers 2,200 beds, distributed between its six specialized institutes and also outpatient services and rehabilitation. The Institute of Geriatrics and Gerontology is located in a very populated area, the east zone of Sao Paulo and is reference for 41 primary health units. The Reference Centre for the Elderly in the North Zone covers 142 primary health care units. The Paula Souza Primary Care Centre is located in the west zone of São Paulo.

The intervention will be delivered in 3 sites: Geriatrics Service at the University of São Paulo Faculty of Medicine Clinics Hospital; the Institute of Geriatrics and Gerontology “José Ermírio de Moraes”; the Reference Centre for the Elderly in the North Zone, where a multidisciplinary team will be trained to deliver the program. Figure 1 describes the study design.

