**Fall risk** will be assessed using the *QuickScreen Clinical Falls Risk Assessment*[37], a validated instrument consisting of five physical performance items, two questions about medications and one about previous falls. An individual’s estimated fall risk will be considered to have decreased if, upon retest, they have moved down to the next level in the risk categories proposed by Tiedemann et al. [37]. The risk categories and their associated probabilities of future falls are as follows: for 0–1 QuickScreen items, the probability of falling is 7%, for 2–3 items the probability of falling is 13%, for 4–5 items the probability of falling is 27% and for 6 or more items the probability of falling is 49%.

**The level of *****difficulty with daily tasks*** will be assessed using the Brazilian OARS Multidimensional Functional Assessment Questionnaire (BOMFAQ) adapted from the Older Americans Resources and Services (OARS) [38] instrument that measures self-reported difficulty while performing 15 daily activity tasks: eight activities of daily living : lying down and getting up from bed, eating, combing hair, dressing, bathing, walking on a uneven surface, getting to the toilet in time, cutting toenails and seven instrumental activities of daily living: taking medications, climbing stairs, walking near home, preparing meals, taking public transport, shopping and cleaning the house, hierarchically organized. The number of activities performed with difficulty will be summed and categorized as follows: 0, 1 to 3, 4–6 or 7 or more activities.

**Services use** will be measured by the number of fall-related visits to emergency departments and hospitalisations (frequency and duration) per participant.

**Compliance** with the home exercise program (frequency and duration) will be recorded in a home exercise diary. Adverse side effects will be measured with an adverse events form, including stiffness, pain, fatigue, etc. At the end of the follow-up period participants will be asked to identify reasons for non-adherence on the home-based exercise program.

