### Sample size calculation

A total of 612 participants (306 per group) will provide 80% power to detect as significant, at the 5% level, a 30% lower rate of falls (i.e. the primary outcome measure) for intervention group participants compared with control participants (i.e., IRR = 0.70). For the sample size calculation we used the gennbreg command in Stata and coefficients from previous studies: alpha (a measure of over-dispersion in the negative binomial regression model) was assumed to be 0.76 based on data from a previous trial [43]. We assumed the control group rate of falls would be 1 fall per person over the 12-month follow-up period. An average follow-up period of 11 months (rather than the planned 12 months) was used in these calculations to account for loss to follow-up.

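### The primary fall-rate model names no baseline covariate; adjusting for past falls, already a planned subgroup variable, would gain a little precision at almost no cost

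*Protocol article*

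**What the plan says.** All references are to the protocol article.

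- **Statistical analysis, primary rate outcome.** Fall incidence in the two groups "will be calculated and compared using negative binomial regression analysis". No covariate is named. The proportion of fallers is compared by a relative risk, again with no covariate.
- **Statistical analysis, secondary outcomes.** General linear models assess the effect of group on the "continuously-scored secondary outcome measures after adjusting for baseline scores".
- **Statistical analysis, subgroups.** "Interactions between subgroup variables (past falls and mobility-related disability) and group allocation will be tested".
- **Trial design.** "Group allocation will take place centrally using a computer-generated permuted block randomisation schedule". No stratification factor is named.
- **Participants.** "Community-dwelling men and women aged 60 and over who have fallen at least once in the last 12 months will be included".
- **Secondary outcome measures.** The fall-risk instrument has "five physical performance items, two questions about medications and one about previous falls".
- **Setting and recruitment.** "Participants will be recruited in 4 referral centers in Sao Paulo, Brazil"; three of these sites deliver the programme.

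**The concern.** The analysis section states baseline adjustment for one class of outcome and names none for the primary outcomes. Past falls is the entry criterion, an item in the risk instrument and a planned subgroup variable, so it is a plausible predictor of later falls. If it predicts them, it accounts for part of the between-person variation that the over-dispersion parameter absorbs. A model that includes it would then estimate the treatment rate ratio more precisely and correct for any chance difference between groups in fall history. On the text, neither the randomisation nor the analysis does this.

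At stake are some precision and some protection against an awkward chance imbalance. There is also a question of timing. The trial was recruiting when the article appeared, and a covariate named before the data are seen cannot be suspected of having been chosen for its effect on the result.

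**Working it through.** **Inputs from the sample size section.** Control rate 1 fall per person over 12 months; rate ratio 0.70; over-dispersion α = 0.76; mean follow-up t = 11/12 year; 306 per group; 5% level. Sidedness is not stated, so two-sided is assumed.

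**1. The plan's own figure.** The section says "A total of 612 participants (306 per group) will provide 80% power to detect as significant, at the 5% level". With the usual Wald formula:

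- V = 1/t + 1/(0.70t) + 2α = 1.091 + 1.558 + 1.520 = 4.169
- SE(log rate ratio) = √(4.169/306) = 0.117
- |ln 0.70|/SE = 0.3567/0.1167 = 3.056; 3.056 − 1.960 = 1.096; power = 86.3%
- n per group for 80% power = (1.960 + 0.842)² × 4.169/0.3567² ≈ 257.2, so 258

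The stated inputs therefore give 258 per group rather than 306. The gap is in the safe direction and does not affect this point. Below, 86.3% is the unadjusted reference.

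**2. Gain from adjustment.** The documents give no prognostic strength, so the share of α explained is an assumption. Adjustment is represented by a smaller residual α, with V = 2.649 + 2α.

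| Share of α explained (assumed) | Residual α | V | V relative to unadjusted | Reduction in SE | Power at 306 per group | n per group for 80% |
|---|---|---|---|---|---|---|
| 0 | 0.76 | 4.169 | 1 | 0 | 86.3% | 258 |
| 10% | 0.684 | 4.017 | 0.964 | 1.8% | 87.6% | 248 |
| 20% | 0.608 | 3.865 | 0.927 | 3.7% | 88.8% | 239 |
| 30% | 0.532 | 3.713 | 0.891 | 5.6% | 89.9% | 230 |

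The gain is worth about 4%, 7% or 11% of the sample.

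**3. What those shares mean for past falls.** Take past falls as 2 or more against 1, with an assumed prevalence p = 0.40 of recurrent fallers and an assumed rate ratio R. The squared coefficient of variation due to the covariate is c² = p(1 − p)(R − 1)²/[1 + p(R − 1)]², and the residual α = 1.76/(1 + c²) − 1.

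- R = 1.5: residual α 0.690 (9% explained)
- R = 2.0: c² = 0.24/1.96 = 0.122; residual α = 1.76/1.122 − 1 = 0.568 (25% explained)
- R = 2.5: residual α 0.453 (40% explained)

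**4. Check by simulation.** 1,500 trials per scenario, 306 per group, p = 0.40, maximum-likelihood negative binomial fits:

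| R (assumed) | Power, unadjusted | Power, adjusted | Average rate ratio, unadjusted / adjusted |
|---|---|---|---|
| 1.5 | 87.9% | 88.5% | 0.696 / 0.697 |
| 2.0 | 85.9% | 87.9% | 0.703 / 0.703 |
| 2.5 | 87.2% | 91.4% | 0.701 / 0.699 |

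Each power figure has a simulation error of about √(0.87 × 0.13/1500) = 0.9 points. The average estimate stays at about 0.70 with or without the covariate. The unadjusted analysis is therefore not biased, and adjustment does not change what is estimated.

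**5. Chance imbalance.** Assume rates of 0.7 and 1.4 for single and recurrent fallers (R = 2, overall mean about 1.0). A 5-point difference between groups in the share of recurrent fallers changes the expected rate by 0.05 × 0.7 = 0.035, so the unadjusted rate ratio moves by about 3% to 4%. The 95% limit for a chance difference at p = 0.40 is 1.96 × √(2 × 0.40 × 0.60/306) = 7.8 points. A difference that large would move the rate ratio by a factor of about 1.03 (R = 1.5) to 1.08 (R = 2.5).

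**The case against.** The best reply is that nothing here is wrong. An unadjusted comparison of randomised groups is unbiased with a valid type I error, and its confidence interval already allows for chance imbalance. A 3% to 4% shift is about 0.035/0.117 = 0.3 of a standard error. Power on the stated inputs already exceeds 80%, and the gain is a few points at most. A covariate list is also something an article may leave to an analysis plan, which is not shown. These points stand, and they make this an optional improvement.

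Four stronger readings are tempting, and the documents do not support them.

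- **That the primary analysis is definitely unadjusted.** The text names no covariate but does not exclude one. The contrast with the secondary outcomes in the same section makes unadjusted the natural reading, no more. Likewise, the article names no stratification factor but does not say that the schedule is unstratified.
- **That past falls is a strong predictor.** Nothing in the documents quantifies it, and its range is restricted because every participant has fallen at least once.
- **That a count of past falls is certainly available.** The quoted screening question is yes/no and is constant among those enrolled. A graded measure must exist for the planned subgroup analysis to be possible, but its form is not given.
- **That adjusting for site brings a measurable gain.** No figure in the documents allows one to be computed. The word is also ambiguous: there are four recruiting centres and three delivery sites, and control participants have no delivery site.

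The adjusted rate ratio keeps its meaning as a single common effect only if the effect does not vary with past falls, which the plan intends to test. That calls for care in reporting and is no reason against adjustment.

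**Conclusion.** The point holds as an inexpensive gain in efficiency and robustness, not as the correction of an error. The article names no covariate for the primary rate model, states adjustment elsewhere in the same section, and names no stratification factor that would compensate. Past falls in graded form is needed for the subgroup analysis in any case.

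The gain is modest: about 1 to 4 percentage points of power, or 4% to 11% of the sample, if past falls explain 10% to 30% of the over-dispersion. Those shares, and the prevalence and rate ratio behind the imbalance figure, are assumptions. The reference power of 86.3% follows from the article's own inputs with a two-sided test.

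**What to change.** Specify the primary model, before the data are examined, as a negative binomial regression of the number of falls on group, with log follow-up time as offset, adjusted for past falls in the graded form recorded for the subgroup analysis (for example 1 against 2 or more). Recruiting centre may be added; if so, say that it means the four recruiting centres and not the three delivery sites. Report the unadjusted rate ratio as a sensitivity analysis.

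If the proportion of fallers is adjusted as well, name a model that keeps the relative risk, such as modified Poisson regression with robust standard errors. A logistic model would replace the relative risk with an odds ratio.

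If an existing analysis plan already lists covariates, it is enough to confirm that they include past falls. The cost is one or two sentences. Adjusting for past falls needs no new data, given that the subgroup analysis already requires a graded measure.

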#### Primary outcome measures

The primary outcome will be the rate of falls and the proportion of fallers in 12 months after randomisation. Participants will receive instructions to fill in a monthly fall diary. They will receive telephone calls each month to ask for information regarding falls and their consequences, such as the mechanisms, environmental conditions, location (indoors or outdoors), activity during the fall and injuries sustained.

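### The proportion of fallers, a primary outcome, is compared by a simple relative risk that ignores follow-up time, so unequal dropout between arms can bias it in either direction

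*Protocol article*

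**What the plan says.** Under Primary outcome measures, the Protocol article sets a fixed window for two outcomes: "The primary outcome will be the rate of falls and the proportion of fallers in 12 months after randomisation".

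Under Statistical analysis, it defines who contributes fall data and for how long: "Fall data will be analysed using all randomised participants until they have died or have withdrawn from the study". The rate of falls is compared by negative binomial regression. For the other outcome the method is: "The proportion of fallers in the two groups will be compared with the relative risk statistic". That sentence contains no follow-up term and no rule for a person who leaves before 12 months without having fallen.

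Under Sample size calculation, incomplete follow-up is expected: "An average follow-up period of 11 months (rather than the planned 12 months) was used in these calculations to account for loss to follow-up".

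**The concern.** The outcome is whether a person falls at least once in 12 months. Someone who withdraws at month 4 without a fall has been observed for a third of that window. If that person stays in the denominator of a simple proportion, the eight unobserved months are treated as free of falls. The rate has a method that can divide by time observed; the proportion of fallers does not.

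The error largely cancels between arms if dropout is the same in both. There is some reason to doubt that it will be. Only the intervention arm is asked for 12 weekly sessions of two and a half hours, a monthly medical evaluation and home exercise twice a week, and participants know their allocation. Control participants, for their part, may lose interest because they are offered little. The direction cannot be known in advance, so the comparison should not depend on it. At stake are the size and the false-positive rate of a result labelled primary.

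**Working it through.** **The plan's own figure.** "A total of 612 participants (306 per group) will provide 80% power to detect as significant, at the 5% level". With mean counts of 11/12 = 0.917 and 0.70 × 0.917 = 0.642 and dispersion 0.76, the usual two-sided Wald formula gives n per arm = (1.96 + 0.84)² × (1/0.917 + 1/0.642 + 2 × 0.76) / (ln 0.70)² = 7.85 × 4.169 / 0.1272 ≈ 258. The stated 306 is therefore not reproduced; it would give about 86% power for the rate. The plan is conservative there, and this does not bear on the present point. I use 306 per arm below.

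**Inputs from the Sample size calculation.** Control rate: "We assumed the control group rate of falls would be 1 fall per person over the 12-month follow-up period". Dispersion: it "was assumed to be 0.76 based on data from a previous trial". Planned rate ratio 0.70. Mean follow-up 11 months.

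**Inputs that I assume.** The dropout split between arms, and leaving times spread evenly over the year. With even spread, each leaver loses 6 months on average, so a mean loss of 1 month implies that 1/6, or about 17%, of participants leave early.

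**Step 1, chance of at least one fall by time t (years).** P(t) = 1 − (1 + 0.76·r·t)^(−1/0.76).
- Control, r = 1, t = 1: 0.525.
- Intervention, r = 0.70, t = 1: 0.430.
- Risk ratio at full follow-up: 0.430/0.525 = 0.82.
- Average of P(t) over t from 0 to 1 at r = 1: 0.319. This is the chance that an early leaver has a recorded fall.

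**Step 2, recorded proportion when a fraction d leaves early.** (1 − d) × 0.525 + d × 0.319.

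**Step 3, no true effect, pooled mean follow-up 11 months, 306 per arm.** The false-positive rate is the two-sided 5% rejection rate by the normal approximation for two proportions.

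| Dropout, control v intervention | Gap (points) | Recorded proportions | RR | False-positive rate |
|---|---|---|---|---|
| 16.7% v 16.7% | 0 | 0.490 v 0.490 | 1.00 | 5% |
| 14.2% v 19.2% | 5 | 0.496 v 0.485 | 0.98 | 6% |
| 11.7% v 21.7% | 10 | 0.501 v 0.480 | 0.96 | 8% |
| 10% v 23.3% | 13 | 0.504 v 0.477 | 0.95 | 10% |
| 5% v 28.3% | 23 | 0.514 v 0.466 | 0.91 | 22% |

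Example, 13-point row: control 0.90 × 0.525 + 0.10 × 0.319 = 0.504; intervention 0.767 × 0.525 + 0.233 × 0.319 = 0.477; ratio 0.95.

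**Step 4, other direction and other timing.** With no true effect, 20% v 10% (control arm losing more) gives 1.04. If all leavers go in the first 3 months, 10% v 20% gives 0.91 with 18% false positives, and 20% v 10% gives 1.09.

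**Step 5, true rate ratio 0.70.** Equal dropout of 1/6 gives 0.815 against a true 0.819. With leavers spread over the year, 10% v 20% gives 0.78 and 20% v 10% gives 0.85.

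**Step 6, methods that use follow-up time.** In simulations with no true effect (500 trials per scenario, leaving unrelated to fall risk), negative binomial regression with a log follow-up offset and a log-rank test on time to first fall both rejected in about 4% to 6% of trials. The simple relative risk rejected in up to 22%.

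**The case against.** The counting rule is an inference. The article never says that an early leaver without a fall is a non-faller, and an analysis plan that is not shown could define the denominator. That is fair as to wording. But the article does name the method for this outcome, and it keeps all randomised participants under intention to treat. Restricting the comparison to completers would conflict with that. Read as written, the text leads to the rule described.

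A reader might infer the stronger claim that dropout here will produce a spurious benefit. The documents do not support it. They give no dropout by arm, and equal dropout is close to harmless. The telephone screen described under Participants asks everyone, before allocation, whether they can attend weekly for 12 weeks. Falls are collected by monthly diaries and calls in both arms, so stopping the classes is not the same as leaving fall follow-up. Large gaps are therefore possible but not predicted, and the gap may run either way.

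The consequence is also limited. The Sample size calculation treats the rate as the primary outcome measure and powers only that, and negative binomial regression can take account of time observed. This stands: the point concerns the proportion of fallers alone.

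**Conclusion.** The point holds in a bounded form. The method named for a primary outcome with a fixed 12-month window takes no account of follow-up that the plan itself expects to be incomplete. The resulting bias requires unequal dropout and can go in either direction. It is small for a 5-point gap (0.98) and modest for 10 points (0.96). Only at a gap of about 23 points (0.91) does it approach half of the planned departure from 1, which is 0.82. Leaving concentrated in the first 3 months makes it larger for the same gap.

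These sizes rest on the plan's rate and dispersion, on assumed dropout splits and leaving times, and on leaving being unrelated to fall risk. The analysis of the rate of falls, the powered outcome, is untouched.

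**What to change.** In Statistical analysis, replace the simple relative risk as the main comparison of the proportion of fallers. Estimate each arm's 12-month risk of at least one fall by Kaplan-Meier from time to first fall, censoring at withdrawal or death, and report the ratio of the two risks with a 95% CI. State the assumption that leaving is unrelated to fall risk. Keep the plain relative risk as a descriptive figure.

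A complementary log-log model with log follow-up as offset should not be presented as equivalent. It estimates a hazard-type ratio: under the planned effect, ln(1 − 0.430)/ln(1 − 0.525) ≈ 0.755, against a 12-month risk ratio of 0.82. Use it only if its results are converted to 12-month risks.

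The cost is a change of wording. Monthly diaries and calls already place falls and the end of follow-up in time, and the article reports that the trial is still recruiting. The small downside is a less familiar statistic.

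### The logistic model for a decrease in fall risk is stated without the baseline QuickScreen count; a group-only model is valid but gives up some power on this secondary outcome

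*Protocol article*

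**What the plan says.** In the Statistical analysis section of the protocol article, general linear models estimate the effect of allocation "on the continuously-scored secondary outcome measures after adjusting for baseline scores". The next sentence reads: "Logistic regression models will be used to compare groups on dichotomous outcome measures". It names no covariate and excludes none. The proportion of fallers is handled separately, by relative risk.

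Under Secondary outcome measures, fall risk is measured with QuickScreen, which has eight items: five physical performance tests, two medication questions and one on previous falls. Risk counts as decreased if at retest "they have moved down to the next level in the risk categories". The bands are 0–1, 2–3, 4–5, and 6 or more items. This is the only outcome in the article that is defined as dichotomous and falls to the logistic models.

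**The concern.** The plan accepts baseline adjustment for one class of secondary outcome and states none for the next, in adjacent sentences. The outcome affected is one where baseline matters by construction, because a participant's distance from the next lower band is set by the baseline item count. If the model contains group alone, that predictable variation stays in the comparison. Power is then lower than the same data could give, and a chance imbalance in baseline count passes into the estimate. At stake is precision on one secondary outcome.

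**Working it through.** **1. What the documents give.** The only computed figure is the primary sample size: "A total of 612 participants (306 per group) will provide 80% power to detect as significant, at the 5% level, a 30% lower rate". Its inputs are a control rate of 1 fall per person-year, an over-dispersion of 0.76, an incidence rate ratio of 0.70 and 11 months of average follow-up. The usual negative binomial formula gives

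n per arm = (1.960 + 0.842)² × [(12/11)(1/1 + 1/0.70) + 2 × 0.76] / (ln 0.70)² = 7.849 × 4.169 / 0.1272 ≈ 257.2, so 258.

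That is 516 in total, not 612; with these inputs 306 per arm has about 86% power (88% by simulation). The stated size is therefore conservative for the primary outcome. It has no bearing on the present point, because no power, baseline distribution or event rate is given for the QuickScreen outcome. Everything below on size rests on assumptions.

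**2. What follows from the bands alone.**

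| Baseline items | Net loss needed |
|---|---|
| 0 or 1 | impossible |
| 2, 4, 6 | 1 |
| 3, 5, 7 | 2 |

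To illustrate, assume that each item present is lost with probability 0.20 and each absent item is gained with probability 0.08, independently. From 2 items, the chance of moving down is 0.92⁶ × (1 − 0.80²) + 6 × 0.08 × 0.92⁵ × 0.20² = 0.218 + 0.013 = 0.23. The same sum gives about 7% from 3 items, 47% from 4, 22% from 5, 68% from 6 and 40% from 7.

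**3. Power by formula.** Assume 275 assessed per arm, a two-sided 5% test and a constant odds ratio within baseline categories. The odds ratio is set so that the group-only test has 80% power. Worked case: 20% in the lowest band, and a 30% control chance of moving down in every other band.

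- Group only: the control proportion is 0.80 × 0.30 = 0.240 and the intervention proportion 0.349. The log odds ratio is 0.531 with standard error √[1/(275 × 0.240 × 0.760) + 1/(275 × 0.349 × 0.651)] = 0.190, so z = 2.80 and power is 80%.
- Adjusted: the conditional odds ratio is 1.81 (log 0.593) and the within-band intervention proportion 0.437. With 0.80 × 275 = 220 informative participants per arm, the standard error is √[1/(220 × 0.30 × 0.70) + 1/(220 × 0.437 × 0.563)] = 0.200, so z = 2.96 and power is 84%.

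The same method in other assumed scenarios, against 80% unadjusted:

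| Scenario | Adjusted power |
|---|---|
| 5% in lowest band, equal chances elsewhere | 81% |
| 10%, equal | 82% |
| 30%, equal | 86% |
| 20%, moderate gradient across bands | 84.5% |
| 20%, steep gradient | 89% |
| Extreme: 40–50% in lowest band, or very strong within-band effect | 93–96% |

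**4. Power by simulation.** Baseline was assumed to be 1 + Binomial(7, p) items with p from 0.25 to 0.50. Item loss was 0.20 versus 0.27, or 0.30 versus 0.38, and item gain 0.08. With 275 per arm, the 0–1 group left out of the adjusted fit and sparse counts merged, adjustment added about 6 to 11 points of power, with type I error at 4–5%. With 306 per arm and the same handling the gain was about 4 to 11 points.

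**5. A trap in the coding.** Entering every baseline count as its own category does not work. The 0–1 category has no events in either arm by definition, and high counts are nearly empty: at p = 0.35 the expected share with all eight items is 0.35⁷, below 0.1%. In simulation, a category with all or no events occurred in 99–100% of trials, and the ordinary maximum-likelihood fit failed or diverged in the same share.

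**The case against.** The strongest reply is that the article is silent, not wrong. It does not specify an unadjusted model, and a condensed article may leave the covariates of a secondary model to an analysis plan that is not shown. That stands against the stronger reading, which a reader might infer, that the plan has decided against baseline adjustment. What remains is that adjustment is stated in one sentence and absent from the next, so the model as written has group as its only term, and a better one is available from data already collected.

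A reader might also infer that the analysis ignores baseline, or that baseline largely decides the outcome. Neither is supported. The outcome is itself a change from the baseline band, and the documents give no distribution or change rates to show how strongly baseline predicts it. Everyone enrolled has fallen in the past year. If the previous-falls item counts any such fall (an assumption), nobody scores 0 and the lowest band holds only those with exactly one item: 13%, 5% and 0.8% under the simulated baselines, from (1 − p)⁷ at p = 0.25, 0.35 and 0.50. The eight items also differ in kind, so equal and independent loss is a simplification. These points limit the size of the gain. They do not remove it, since position within a band matters even where the lowest band is almost empty.

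Finally, a reader might infer bias. Randomisation keeps the group-only test valid, and its simulated type I error was 4.8%.

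**Conclusion.** The point holds as an efficiency matter on one secondary outcome for which the trial was not sized. The bands make success depend on the baseline item count, and a logistic model that includes the count is more powerful than one with group alone. The gain is roughly 1 to 11 points of power under plausible assumed values, up to 16 (80% to 96%) in extreme scenarios, and as little as 1 when few participants sit in the lowest band and the other bands behave alike. These figures depend on assumed baseline distributions, item-change rates and numbers assessed. The primary outcome is unaffected. Severity is low.

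**What to change.** State in the Statistical analysis section that the logistic model for a decrease in fall risk includes the baseline QuickScreen item count as categories, with sparse high counts merged, for example 2, 3, 4, 5, and 6 or more. Participants with 0 or 1 items at baseline have no possible event and add nothing to the adjusted odds ratio. Leave them out of that fit, which is safe because the exclusion rests on a pre-randomisation value, or use a penalised fit.

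Also report a standardised risk difference or risk ratio over all assessed participants. Average each person's predicted probability under each allocation, with the 0–1 group counted as non-events in both.

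The cost is a few sentences and no new data. There are two downsides: the odds ratio becomes conditional on baseline, which the standardised measure offsets, and the handling of the 0–1 group must be written out. Recruitment is described as under way, so the change can be fixed before outcome data are analysed.
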